### 2.2. Sample and Participants

#### 2.2.1. Sample Size

The sample size was determined based on the comparison between the two individually randomized study arms. The original calculation was based on a standardized difference of d = 0.50. A previous assessment of the same workshop population showed a standard deviation of approximately 0.197 for the EQ-5D index. Therefore, d = 0.50 corresponds to an absolute difference of approximately 0.10 EQ-5D index units. This correspondence is provided solely to contextualize the standardized effect used in the original sample-size calculation and is not a decision threshold for intervention effectiveness.

Using G*Power version 3.1.9.6 (Heinrich Heine University Düsseldorf, Düsseldorf, Germany) (two-tailed independent-samples *t*-test, α = 0.05, power = 0.80, 1:1 allocation, and standardized effect size d = 0.50), a total sample size of 128 participants, 64 per arm, was obtained. The complementary calculation for paired samples yielded a smaller sample size requirement and, therefore, did not determine the final sample size.

Because the primary endpoint is assessed at 1 month, the recruitment target was set to protect the primary analysis against the missing primary-outcome data at this time point. Based on previous workshop experience, approximately 20% of the randomized participants may fail to provide the 1-month assessment. Compensating for this anticipated loss requires 160 participants (128/0.80 = 160). To provide an additional operational margin for unanticipated missingness and later follow-up, this study will aim to recruit 180 participants (90 per arm). Later attrition may accumulate over the longer follow-up, but the 4-month and 7-month analyses are secondary or exploratory and do not determine the sample size for the primary endpoint.

Although the intervention is delivered in workshop groups, randomization is performed at the individual level and clustering occurs only in the intervention arm. A conventional cluster-randomized design effect, therefore, will not be applied. No empirical workshop-specific ICC was available to support a formal ICC-based inflation. Potential workshop-level correlation will be addressed prospectively using the prespecified partially nested mixed-effects model. The target of 180 participants provides additional recruitment margin beyond the formal individual-level requirement but is not presented as a formal ICC-adjusted power calculation.

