### 2.5. Data Analysis

#### 2.5.1. Quantitative Analysis

Statistical analysis will be performed using IBM SPSS Statistics, version 27.0 (IBM Corp., Armonk, NY, USA). For categorical variables, absolute frequencies and percentages will be calculated. For quantitative variables, means and standard deviations (SDs) or medians and interquartile ranges will be reported, depending on whether the variables follow a normal distribution. This study has a single confirmatory primary analysis: the baseline-adjusted between-group difference in the EQ-5D index at 1 month, evaluated at a two-sided α level of 0.05. The EQ-5D contrast at 4 months and the prespecified secondary outcomes will be treated as supportive secondary analyses. Analyses of ad hoc outcomes, treatment-effect modification, subgroup analyses, per-protocol analyses, and the month-seven maintenance assessment will be considered exploratory. No global formal adjustment for multiplicity will be applied to these secondary and exploratory analyses because they will not be used to support independent confirmatory claims. Effect estimates and 95% confidence intervals will be emphasized; *p* values for secondary and exploratory analyses will be reported as nominal and interpreted cautiously in the context of multiple testing, and isolated nominal *p* values < 0.05 will not be considered confirmatory evidence.

Continuous secondary outcomes measured repeatedly will be analyzed using analogous linear mixed-effects models. Binary outcomes will be analyzed using logistic generalized linear mixed-effects models; count outcomes will be analyzed using Poisson or negative-binomial mixed-effects models, according to dispersion; and ordinal outcomes will be analyzed using an appropriate ordinal mixed-effects model when applicable.

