The primary analysis will follow the intention-to-treat principle. All of the randomized participants will be analyzed in the group to which they were originally assigned, regardless of their adherence to the intervention. The participants attending fewer than four workshop sessions will be classified as non-adherent, but will not be considered lost to follow-up and, unless they withdraw consent, will continue to be invited to complete the scheduled outcome assessments and will remain included in the intention-to-treat population. Intervention discontinuation, adherence, and loss to outcome follow-up will be recorded separately. Longitudinal mixed-effects models will use all available outcome measurements and will be estimated by maximum likelihood under a missing-at-random assumption. Intervention discontinuation, adherence, and loss to outcome follow-up will be recorded separately. If outcome data are missing, multiple imputation under a missing-at-random assumption will be used as a prespecified sensitivity analysis, including treatment allocation, baseline outcome values, available repeated outcome measurements, relevant baseline prognostic variables, and available information related to attendance/adherence and missingness.

When sample size allows, quantitative results will be described, disaggregated by sex, and potential differences in primary and secondary variables will be explored. Sex will be included as a prespecified exploratory effect modifier. For longitudinal outcomes, the treatment × sex and treatment × visit × sex interactions will be assessed. Where the data permit, adjusted intervention effects will be presented separately by sex, with 95% confidence intervals. These analyses will be considered exploratory, as this study was not specifically powered to detect interaction effects.

Given that the participants in the intervention arm receive the intervention in workshop groups, and that all workshop sessions are conducted at the same study center using the same structure and standardized procedures, a workshop-level random effect will be considered within the intervention arm to account for potential residual correlation and heterogeneity across workshop sessions. The structure is partially nested, as the participants in the control group are not assigned to workshops.

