The participants who do not complete the 4-month questionnaires will be considered lost to follow-up. Their sociodemographic and clinical characteristics, as well as their baseline scale scores (included in the baseline assessment), will be analyzed to characterize the profile of these patients. If, during follow-up, a participant from either the control or intervention group modifies their medication or the therapies they receive, they will not be considered lost to follow-up; they will remain in this study, and changes will be assessed at 1, 4, and 7 months. The patients originally assigned to the control group will not be included as part of the intervention group in this study. Although they will be offered the opportunity to participate in a workshop after completing their follow-up as controls, they will not be considered part of the intervention group for study purposes.

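### The named missing-data sensitivity analysis keeps the missing-at-random assumption of the primary model, so nothing stated tests departure from it at month 1; separately, the attrition profile is built on month 4

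*Protocol article*

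**What the plan says.** The single confirmatory analysis in section 2.5.1 is "the baseline-adjusted between-group difference in the EQ-5D index at 1 month, evaluated at a two-sided α level of 0.05". Section 2.2.1 states that "approximately 20% of the randomized participants may fail to provide the 1-month assessment" and enlarges the sample for it: "Compensating for this anticipated loss requires 160 participants (128/0.80 = 160").

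On missing outcomes, section 2.5.1 gives two methods:

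- **Main model:** "Longitudinal mixed-effects models will use all available outcome measurements and will be estimated by maximum likelihood under a missing-at-random assumption".
- **Sensitivity analysis:** "multiple imputation under a missing-at-random assumption will be used as a prespecified sensitivity analysis". Its variables include allocation, baseline and repeated outcomes, prognostic variables, and whatever is known about attendance and missingness.

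The only other sensitivity analysis named is per-protocol (section 2.1.3, classed as exploratory in section 2.5.1). It concerns adherence, not missing outcomes.

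On attrition, section 2.5.1 says: "The participants who do not complete the 4-month questionnaires will be considered lost to follow-up". The baseline characteristics of those participants are then to be described.

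**The concern.** A missing-data sensitivity analysis is most useful when it relaxes the assumption that the main analysis cannot verify. Here that assumption is MAR: given the observed data, those who did not answer would have scored like those who did. The imputation widens the set of observed variables but keeps the assumption. Dependence on the unobserved month-1 score itself stays untested.

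The document gives reasons to doubt MAR. The Limitations section expects losses from the length of the workshop and the need to attend in person, which during the comparative period apply only to the intervention arm. Table A1 has that arm complete its scales within session 5, with help from facilitators, whereas controls answer through the app. Participants are unblinded and the outcome is self-reported. Month-1 missingness may therefore differ by arm and be related to outcome. Enlarging the sample from 128 to 160 restores precision but does not address bias.

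The attrition profile is a separate, smaller matter. A participant with a month-1 EQ-5D but no month-4 questionnaire counts as lost. One who misses month 1 and returns at month 4 does not. The profile therefore does not describe the people missing from the primary endpoint.

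**Working it through.** **Inputs from the protocol**

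- Section 2.2.1: "α = 0.05, power = 0.80, 1:1 allocation, and standardized effect size d = 0.50"; "standard deviation of approximately 0.197 for the EQ-5D index"; 20% missing at month 1; 160 participants needed and 180 targeted.
- Section 2.3.1: 0.03 to 0.10 is given as the range of clinically relevant EQ-5D index change. It is used here only as a scale for the departure from MAR.

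**Assumptions, not in the protocol**

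- The missing share in the intervention arm, f, is 0.20 (range 0.10 to 0.30). The protocol gives no figure by arm.
- Missing intervention participants score lower than MAR predicts by delta; missing controls follow MAR.
- The standard error is unadjusted and held fixed. Baseline adjustment would shrink it and workshop clustering would widen it.

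**Step 1: the plan's own figures**

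The exact two-sample t-test with d = 0.50 gives 64 per arm (power 80.1%), 128 in total. 128/0.80 = 160. d = 0.50 is 0.50 × 0.197 = 0.0985 index units. All reproduce.

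**Step 2: precision**

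With 20% missing, completers per arm are 160 × 0.80/2 = 64 or 180 × 0.80/2 = 72.

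- 64 per arm: SE = 0.197 × √(2/64) = 0.0348; 1.96 × SE = 0.0683.
- 72 per arm: SE = 0.197 × √(2/72) = 0.0328; 1.96 × SE = 0.0644.

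Using t quantiles the half-widths are 0.0689 and 0.0649, which lowers the tipping values in step 4 by about 0.003 at f = 0.20.

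**Step 3: effect of a departure**

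Adjusted difference = MAR difference − f × delta.

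| delta | shift, f = 0.10 | shift, f = 0.20 | shift, f = 0.30 | power, 64 per arm (f = 0.20) | power, 72 per arm (f = 0.20) |
|---|---|---|---|---|---|
| 0 | 0 | 0 | 0 | 80.1% | 84.6% |
| 0.03 | 0.003 | 0.006 | 0.009 | 75.0% | 79.9% |
| 0.05 | 0.005 | 0.010 | 0.015 | 71.3% | 76.3% |
| 0.10 | 0.010 | 0.020 | 0.030 | 60.9% | 66.1% |

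Power is for a MAR difference of 0.0985 reduced by the shift.

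**Step 4: tipping point**

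Tipping delta = (observed difference − 1.96 × SE)/f.

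| observed difference | f | 64 per arm | 72 per arm |
|---|---|---|---|
| 0.0985 | 0.20 | 0.151 | 0.171 |
| 0.08 | 0.20 | 0.059 | 0.078 |
| 0.0985 | 0.30 | 0.101 | 0.114 |
| 0.08 | 0.30 | 0.039 | 0.052 |
| 0.0985 | 0.10 | 0.302 | 0.342 |
| 0.08 | 0.10 | 0.117 | 0.157 |

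**Step 5: no benefit among the missing**

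If intervention completers gain 0.0985 over control and the missing 20% gain nothing, the effect in all randomized is 0.0985 × 0.80 = 0.0788. MAR then overstates it by 0.0197, and the result still exceeds both half-widths. From an observed 0.08, 0.08 × 0.80 = 0.064, which falls just below them.

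**The case against.** The strongest reply is that the planned imputation is not a copy of the main model. It uses attendance, which the protocol does not list for the mixed model, and those attending fewer than four sessions are still invited to assessments. Suppose 25% of the intervention arm do not adhere and gain nothing, and 80% of them are missing, so 0.25 × 0.80 = 20% of the arm is missing. The true effect is 0.0985 × 0.75 = 0.074. Ignoring attendance gives 0.0985 × 0.75/0.80 = 0.092. Conditioning on attendance can recover 0.074 from the non-adherers who did respond. A reader might infer that the two methods must agree, or that attendance cannot enter the imputation because controls have none. Neither follows: attendance can be used within the intervention arm. This part of the reply stands. Its limit is that attendance cannot help if nearly all non-attenders are missing, or if missingness depends on the unseen score among people with the same attendance.

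A reader might also infer that the bias must favour the workshop. The document gives no missingness by arm. Intervention attenders have a supervised slot for the scales while controls rely on the app with reminders and support, so loss could instead fall on controls, with unknown sign.

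A reader might infer that the month-4 definition is what leaves the primary outcome unchecked. It is not. It governs a description only, and month-4 values of those who return enter both the mixed model and the imputation.

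Finally, the full analysis plan is not shown and could contain more. That is fair, and imputation detail alone would be no finding. But the article names its prespecified sensitivity analysis and fixes its assumption, and that choice can be judged as written.

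**Conclusion.** The point holds in moderate form. Both stated methods assume MAR, and no stated analysis tests departure from it for the roughly 20% of month-1 values expected to be missing. With 20% missing in the intervention arm and a departure of 0.03 to 0.10 in that arm only, the estimate falls by 0.006 to 0.020.

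The stronger reading, that missing data at the planned rate would overturn a result of the size the trial was designed for, is not supported. At 0.0985 the tipping departure is 0.15 to 0.17, outside that range. At an observed difference near 0.08 it is 0.06 to 0.08, inside the range, so conclusions there could change. These figures rest on the assumed arm-specific missing share, the one-sided departure and an unadjusted standard error. The sample-size arithmetic is correct.

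The month-4 attrition profile is a separate mismatch with the month-1 endpoint. It affects description, not who enters the primary analysis.

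**What to change.** 1. Keep the planned MAR imputation, run separately by arm, with attendance used in the intervention arm.
2. Add a delta-adjusted analysis: subtract delta from the imputed month-1 EQ-5D values in the intervention arm, over a grid wide enough to reach the tipping point (for example 0 to 0.20, extended if few values are missing), and report where significance is lost.
3. Add an analysis that imputes missing intervention participants from the control-arm distribution.
4. Define primary-outcome loss as no month-1 EQ-5D, report it by arm, and profile those participants. Keep the month-4 profile for the secondary 4-month analysis.

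All of this should be fixed before the allocation codes are opened to the analyst. The cost is a little more analysis work, with no new data, no extra participants and no change to the primary analysis. The downside is that a less favourable scenario will be reported beside the main result.

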#### 2.5.2. Qualitative Analysis

The qualitative strand will adopt a descriptive phenomenological approach grounded in Husserlian phenomenology and operationalized according to Giorgi’s descriptive phenomenological method. This approach was selected because the qualitative component aims to describe the participants’ lived experiences following the intervention and to understand the meaning they attribute to the techniques learned and their incorporation into everyday life.

The qualitative analysis will be supported by ATLAS.ti, version 26 (ATLAS.ti Scientific Software Development GmbH, Berlin, Germany).

Following Giorgi’s approach, the analysis will involve: (1) reading each transcript in its entirety to obtain a sense of the whole experience; (2) identifying meaning units relevant to the phenomenon under study; (3) transforming these meaning units into phenomenologically sensitive expressions while remaining grounded in the participants’ accounts; and (4) synthesizing the transformed meaning units to describe the general structure of the participants’ experience. Throughout the analytical process, researchers will adopt a reflexive phenomenological attitude and will seek to bracket prior assumptions regarding chronic pain and the intervention.

Sex/gender will be considered as a cross-cutting interpretive axis in the qualitative analysis. Attention will be paid to differences in the experience of pain, caregiving roles, barriers to self-management, participation in the workshop, and perceived usefulness of the techniques learned.

The analysis will be conducted independently and subsequently discussed by two external researchers who are not involved in the organization or delivery of the workshop.

The qualitative findings will be used to explain the quantitative results and to identify potentially useful information not captured by the scales and questionnaires administered. Integration will take place in Section 3.

### 2.6. Rigor, Validity, and Reliability

The quantitative and qualitative strands of this study were designed and will be reported according to their respective standards: SPIRIT [42] and CONSORT [43] for the randomized trial, and SRQR [44] and COREQ [45] for the qualitative study based on semi-structured interviews. The intervention was described in accordance with the Template for Intervention Description and Replication (TIDieR) checklist [46], which is provided in Supplementary Materials.

The methodological quality of the quantitative strand will be ensured by the use of validated instruments to assess the main study variables. These include the EQ-5D for health-related QoL [27], the Numerical Rating Scale for pain intensity [28], the Rosenberg Self-Esteem Scale [29], the BRS for resilience [30,31], the HADS for anxiety and depression [32], and the PCS for pain catastrophizing [33]. Data collection will be standardized across the predefined assessment time points for both groups during the comparative period. In addition, the intervention will follow a homogeneous structure in terms of sessions and content, and adherence will be monitored through attendance records. To reduce the risk of bias in between-group comparisons, the researcher responsible for the quantitative data analysis will remain blinded to the participants’ allocation.

In the qualitative strand, rigor will be addressed according to Lincoln and Guba’s quality criteria, including credibility, transferability, dependability, and confirmability. Participants with different sociodemographic profiles will be included to capture a sufficient diversity of experiences and perceptions regarding the intervention. The analytical process, including decisions related to coding, categorization, and interpretation, will be documented in detail to enhance the traceability of the analysis and allow it to be reviewed.

## 3. Discussion

This protocol describes a mixed-methods study designed to evaluate a structured multicomponent workshop based on NPhTs for patients with chronic non-cancer pain. This study addresses the need to assess this type of intervention using a more robust design than previous non-randomized evaluations of the program [21]. It also incorporates a qualitative strand to explore participants’ experiences, the perceived usefulness of the techniques, and the factors that may facilitate or hinder their integration into everyday life.

The mixed-methods approach is a strength of this study. The quantitative results will allow comparison between the intervention and control groups during the comparative period. The qualitative data will provide a deeper understanding of how participants perceive the intervention and incorporate the tools learned into their daily lives. Together, these approaches will provide complementary perspectives on the effects of the intervention and participants’ experiences.

The multicomponent and multidisciplinary approach may support the integration of structured NPhTs into person-centered care models oriented towards self-care. In addition, the group-based, face-to-face format may promote peer support and shared learning. These elements are relevant in CP care, where education, emotional regulation, lifestyle-related strategies, and sustained self-care may need to be addressed together rather than as isolated components.

From an operational perspective, this study will require coordination between hospital services and primary care professionals to identify and refer potentially eligible patients. The face-to-face group format also requires appropriate planning of the sessions, the availability of a suitable space, and coordination among the professionals involved. To support intervention fidelity and rigor in the analysis of the results, the workshop will follow a standardized structure and content across the different editions.

Although this study will be conducted in a hospital setting, the intervention does not require complex clinical equipment. However, its implementation requires trained professionals, multidisciplinary coordination, repeated face-to-face sessions, and digital support. These requirements, together with the single-center setting and the specific expertise of the multidisciplinary team, should be considered when assessing transferability. The program may be adaptable to other healthcare settings, such as primary care centers or pain units, although its transferability will need to be evaluated in different organizational and clinical contexts.

The mobile application is conceived as a support tool after the face-to-face workshop. It is intended to reinforce continuity in the use of the techniques learned during the sessions. It is not intended to replace the interpersonal and group-based components of the intervention, but rather to help the participants maintain self-care strategies once the sessions have ended. However, differences in digital literacy, access to suitable mobile technology, and engagement with the application may influence its use, adherence to the digital component, and the completeness of app-based data.

Incorporating a gender perspective may contribute to a more contextualized interpretation of the experience of CP and responses to group-based therapeutic education interventions. The interpretation of effectiveness will be guided primarily by the prespecified primary outcome, while secondary outcomes will provide complementary information on specific domains. Given the number of secondary outcomes, these findings should be interpreted cautiously, considering the magnitude and clinical relevance of the observed changes rather than statistical significance alone.

